### **6. Study instruments**

#### **6.1 Questionnaire**

A brief questionnaire will be developed to collect weight, medical and menstrual history, for comparison of other side effects as per the secondary objective (Appendix 3 case record form). This is a closed-ended questionnaire which covers all possible answers per question. The type of questions enables the generation of numeric data. The screening CRF includes eligibility check. The enrolment CRF includes medical gynaecological history, history of contraceptive use, data about HIV status, weight, and menstruation.

#### **6.2 Beck Depression Inventory (BDI-II)**

The Beck Depression Inventory is selected to evaluate depressive symptoms. It has been previously validated, used in the same cultural context and translated into the local languages IsiXhosa and IsiZulu. English, IsiZulu and IsiXhosa versions of the BDI-II will be used in this study. The BDI-II can be self administered or verbally administered by a trained administrator. In this study, verbal administration will be utilised during study follow-up interviews. The BDI-II has 21 items, and each item is rated on a four-point scale ranging from 0-3. The maximum total score is 63. According to the BDI-II manual, scores of 0-13 indicate minimal depression, scores of 14-

19 indicate mild depression, scores of 20-28 indicate moderate depression, and scores of 29-63 indicate severe depression. See appendix 2 and 3 for a copy. If participants have high scores indicating severe depression they will be referred to a Psychologist and if unresolved referral to a Psychiatrist will be done.

### **6.3 Arizona Sexual Experience Scale**

The Arizona Sexual Experiences Scale (ASEX) is used to evaluate sexual functioning. This is a five-item rating scale instrument with total scores ranging from 5–30. It has been validated to be independent of the presence of a sexual partner, and can therefore be used even when study participants are not sexually active. Questions 4 and 5 of this scale are not ranked if a participant has not engaged in sexual intercourse within a week of the interview. See appendix 4 for a copy.

### **6.4 28 Days daily Dairy**

Participating women will be asked to prospectively complete a 28-day daily diary at home of symptoms and behaviour, commencing on the day of their month 6 visit. A daily diary has been used in other studies that measure daily symptoms potentially related to the hormone fluctuations in women. Parameters measured in the daily diary include sexual interest, activity and condom use, mood, and characteristics of menstruation. To optimize compliance and the quality of self-reporting, research staff will show participants how to complete the daily diary by assisting them to complete their 'day 1' entries.

## **7. Project management**

The Trial PIs, professional nurses and field workers who will be working as researchers will undergo a Good Clinical Practice course before they work on this trial. The site PIs will do regular checks to ensure that the field workers (trained research assistants) are practising according to the Good Clinical Practice Guidelines. Overall project management will be the responsibility of each site PI. Quality control will be monitored by external audits.

### **7.1 Data quality assurance**

Clinical Research Forms (CRFs) will be designed and produced by the study team on site in consultation with SA MRC. CRFs will be used to collect information for statistical analysis. The study database will be constructed by SA MRC statistical services. Internal quality control will be on-site both by a second member of the research team checking forms for correct completion.

Range checks, plausibility and consistency checks will be built into the database entry system to assess consistency, accuracy and completeness of the data collected.

Guidelines will be prepared for interviewing and collecting data. If feasible, direct data entry such as REDCap will be used. Alternatively, paper CRF's will be used. The guidelines will list all data management activities and specify the roles and responsibilities of all personnel involved in the study. The local study staff will be trained in data collection, interviewing techniques and online data entry. Standard ASCII or SAS datasets will be generated from the final study database for analysis.

Study training will be carried out at each of the study sites for all members of the research team on data collection and study techniques. Specifically, participating research team members will be trained to correctly describe the study to potential participants, administer the screening and consent forms, collect contact data from participants, and correctly fill out study forms. Training will be repeated as required.

## **8. Data management**

The SA MRC, will provide data management and statistical support for the trial. Data will be collected by research staff onto tablets or paper case record forms. The data will be entered on site onto a web based, fully GCP compliant data management system, which will be used for data entry and data validation. SA MRC will provide hosting for the system and data backups.

### **8.1 Confidentiality of data**

Confidentiality of participant information will be assured by the following measures:

- Trial data will be entered onto CRF's with the participant's trial ID number, not name.
- Trial documents will be kept securely under lock and key in the research offices and not be accessible other than to the researchers
- Data will be entered by trial ID number onto a password-protected database to which only trial staff will have access.
- The trial report will not contain names of any participants
- After completion of the trial, the trial documents (Hard copies) will be kept for 2 years under lock and key and electronic archiving will be done for 15 years .
- Forms such as locator forms which records names and other personal identifiers will be stored separately from the study records identified by codes. All records will be stored securely in a locked file cabinet which has limited access.

### **8.2 Data analysis plan**

Analysis will be by intention to treat, and the results will be reported according to the CONSORT guidelines. Baseline characteristics will be compared to confirm the effectiveness of the

randomization process. Numbers and baseline characteristics of losses to follow-up will be compared between groups to detect any imbalances in loss to follow-up. Number of subjects, number of missing values and percentages will be reported for categorical variables. Number of subjects, number of missing values, minima, maxima, means and standard deviations will be reported for continuous variables. Appropriate transformation of non-normal or skewed measurement will be performed on continuous variables. If transformations do not generate a distribution approaching normality, medians and IQR will be reported.

For incidence outcomes (eg pregnancy and HIV seroconversion) with varying duration of follow up between groups, data will be adjusted for duration of follow up.

Categorical variables will be compared as risk ratios with 95% confidence intervals. For continuous data, mean differences with 95% confidence intervals will be reported.

The primary analysis will be based on all subjects with outcome data available. A sensitivity analysis will be performed that only analyzes participants who have neither discontinued nor switched contraceptive methods to assess the impact of switching and discontinuation.

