## Methods

HIV negative women between the age of 18-40years attending family planning services or the research sites will be fully counselled on all available contraceptive options. Those who request IP and meet the eligibility criteria will be informed of the trial and offered participation. Baseline demographic, psychological, physiological and behavioural data will be recorded. Baseline blood and genital tract samples for immunological and hormonal studies will be collected. Participants will be allocated by an online randomization service to one of the 2 IP options, and receive their first injection. A 28-day daily symptom and behaviour diary will be initiated at month 6 to be returned at month 7, 8 or 9. If funds are permitted we will use an sms system for participants to complete the daily diary. Blood will be collected for immunological and hormone studies at baseline month 0, month 6 and at month 6+7days. Subject to funding, HIV PCR will be measured at 18 months.

Sample size was calculated based on the expected standard deviation of key continuous outcomes, (221 participants per group), and allowing for 15% loss to follow-up, will be 260 per group.

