#### **4. Study outcomes:**

##### **4.1 Primary outcomes**

The primary hormonal outcome will be serum 17 $\beta$  estradiol, and the primary psychological outcome will be depression (BDI-II). The study will be powered to measure a difference of 35 pmol/L in the mean serum 17 $\beta$  estradiol between arms, and a difference of 2 in the mean depression scores (BDI-II). The other measures will be regarded as exploratory.

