**Table 1: Screening and Enrolment activities**

| Activities                                                      | Staff                 |
|-----------------------------------------------------------------|-----------------------|
| Notice information +IC – [15-30min]
Locator information      | Counselor             |
| Eligibility assessment (CRF1 Scr) - [15min]
Demographic data | Study Nurse           |
| HIV counselling and test – [30min]                              | Counselor             |
| Clinical interview (CRF2) - [30min]                             | Clinician/Study Nurse |

|                                                             |                       |
|-------------------------------------------------------------|-----------------------|
| Clinical assessment (CRF3) - [30-40min]                     | Clinician/Study Nurse |
| Anthropometric measures (height,weight)
(CRF3) - [10min] | Clinician/Study Nurse |
| BDI-II & ASEX - [15min]                                     | Counselor             |
| Blood and genital tract sample collection* -
[30min]     | Study nurse           |
| Randomisation                                               | Study nurse           |

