### 5.8.3 Randomization procedure

Allocation lists will be prepared by SA Medical Research Council (MRC) using computer-generated random sequence in balanced blocks of variable size, stratified by study site. Women who agree to participate will be entered onto a trial register and then randomized by accessing an online randomization service hosted by SA MRC. In the event of difficulty accessing the online service, a separate series of randomized allocations will be available in sequentially numbered, sealed opaque envelopes, or by telephone back-up service. Every effort will be made to use the back-up system only when essential. The point of trial entry will be the online group allocation or opening of the envelope.

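### Section 8.2 names no baseline or site term for the primary mean differences, although both are available; the comparison is valid as written but may forgo precision

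*Protocol*

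**What the plan says.** Section 8.2 of the protocol sets the effect measure for continuous outcomes: "For continuous data, mean differences with 95% confidence intervals will be reported". It sets the analysis set: "The primary analysis will be based on all subjects with outcome data available". The only adjustment it names is for incidence outcomes such as pregnancy and HIV seroconversion, where "data will be adjusted for duration of follow up". Baseline data have two stated uses. One is a check on allocation ("Baseline characteristics will be compared to confirm the effectiveness of the" randomisation process); the other is a comparison of women lost to follow-up.

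The material for an adjusted analysis is already collected:

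- **Baseline BDI-II.** Table 1 (section 5.8.2) lists "BDI-II & ASEX - [15min"] among the enrolment activities, ahead of randomisation.
- **Baseline hormones.** The Project Summary, Methods, says "Blood will be collected for immunological and hormone studies at baseline month 0, month 6 and at month 6+7days". Section 5.8.2 also lists baseline blood for hormonal studies. Neither place names estradiol, but it is the primary hormonal outcome.
- **Site.** Section 5.8.3 describes a "computer-generated random sequence in balanced blocks of variable size, stratified by study site".

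Section 5.6 sizes the trial as a two-sample comparison of means, with no allowance for baseline correlation or site.

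**The concern.** Section 8.2 is the protocol's data analysis plan. Followed as written, it compares arm means with no use of the baseline value of the same measure and no use of the randomisation stratum. That has two consequences.

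First, the part of the follow-up variance that baseline could explain stays in the error term. BDI-II has no reserve to spare, because 221 evaluable women per group gives just 80% power at the assumed SD.

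Second, blocking within site balances the arms across sites. If mean scores differ between sites, that balance makes the true sampling variance of the difference smaller than the ordinary two-sample standard error suggests, and the confidence interval comes out too wide. A site difference is plausible. The sites lie in two provinces (sections 2.5 and 5.2), each is expected to supply half the women (section 5.5), and BDI-II is given verbally in three languages (section 6.2).

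Precision on the two primary outcomes is at stake, not bias or the validity of the comparison.

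**Working it through.** **1. Inputs from section 5.6.** Depression: difference 2, SD 7.5, 221 per group, 260 after 15% loss. Estradiol: difference 35 pmol/L, SD 119, 181 per group, 213 after 15% loss. I read 95% certainty as two-sided alpha 0.05; power is 80%. The SD of 7.5 was observed on MADRS, not BDI-II, and every BDI-II figure below carries that assumption.

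**2. Reproducing the plan's figures.** n per group = 2 × (1.960 + 0.8416)² × SD² / difference².

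- Depression: 2 × 7.849 × 56.25 / 4 = 220.7, so 221; 221 / 0.85 = 260. Exact match.
- Estradiol: 2 × 7.849 × 14161 / 1225 = 181.5, which is 182 rounded up against 181 stated; 181 / 0.85 = 212.9, so 213. Agrees within rounding.

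The stated sizes are those of an unadjusted comparison and do not rely on adjustment.

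**3. Unadjusted power.** Power = Φ(difference / (SD × √(2/n)) − 1.960).

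- BDI-II at 221: 2 / (7.5 × √(2/221)) = 2 / 0.7135 = 2.803; Φ(0.843) = 80.0%.
- Estradiol at 221, the number per group the trial plans to have evaluable: 35 / (119 × √(2/221)) = 35 / 11.32 = 3.092; Φ(1.132) = 87.1%.

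**4. Adding the baseline value.** With correlation r between baseline and follow-up, the ANCOVA residual SD is approximately SD × √(1 − r²). The protocol gives no r, so the values are assumptions.

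| Assumed r | √(1 − r²) | BDI-II power, n = 221 | BDI-II n per group for 80% | Estradiol power, n = 221 |
|---|---|---|---|---|
| 0 | 1.000 | 80.0% | 221 | 87.1% |
| 0.1 | 0.995 | 80.4% | 219 | 87.4% |
| 0.3 | 0.954 | 83.6% | 201 | 90.0% |
| 0.5 | 0.866 | 89.9% | 166 | 94.6% |
| 0.7 | 0.714 | 97.5% | 113 | 99.1% |

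The same r need not apply to both outcomes. For estradiol it is probably lower: the baseline sample precedes the first study injection, the protocol sets no menstrual-cycle timing for it, and month 6 is on treatment.

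**5. Ignoring the stratum.** Let site explain a share f of the outcome variance (again assumed). With balance within site, the true standard error of the difference is √(1 − f) times the one a two-sample test uses. Actual type I error = 2 × (1 − Φ(1.960 / √(1 − f))). Unadjusted BDI-II power = Φ(0.843 / √(1 − f)). Site-adjusted power uses SD × √(1 − f) in the formula of step 3.

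| Assumed f | 1.960 / √(1 − f) | Actual type I error | BDI-II power, site ignored | BDI-II power, site adjusted |
|---|---|---|---|---|
| 2% | 1.980 | 4.8% | 80.3% | 80.8% |
| 5% | 2.011 | 4.4% | 80.7% | 82.0% |
| 10% | 2.066 | 3.9% | 81.3% | 84.0% |

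The error is in the conservative direction, and small unless site matters a good deal.

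**The case against.** The strongest reply is that section 8.2 states a reporting format, not a model. An ANCOVA estimate is also a mean difference with a 95% confidence interval, and covariates are routinely left to the SAP, which is not at hand. A reader might infer that the protocol commits the trial to an unadjusted primary analysis. The text does not support that: it never uses the word, and silence is not a decision. What remains is narrower. Section 8.2 does name adjustment where it wants it (incidence outcomes), gives baseline data other uses, and sits beside a sample size for a plain comparison. Read alone, it leads to the less precise analysis.

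The second reply is that nothing is broken. This stands. The two-sample comparison is valid in a 1:1 randomised trial, the sample size fits it, and ignoring site errs conservatively.

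The third reply is that the gain is assumed. This also stands. At a correlation of 0.1 the BDI-II gain is 0.4 percentage points. A reader might go further and argue that adjustment is needed to rescue BDI-II power if its SD exceeds the MADRS value. The protocol gives no BDI-II SD, so that argument cannot be sized here and is a separate matter.

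**Conclusion.** The point holds as an available improvement in efficiency and pre-specification, not as an error. The protocol collects baseline BDI-II and a baseline hormone sample, stratifies by site, and uses none of these in the primary comparison as section 8.2 describes it. A reader might infer that the trial is underpowered or its primary analysis unsound. Neither follows, since the stated 80% power is met without adjustment.

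For BDI-II the gain at 221 per group runs from under half a percentage point to about 17 points (80.0% to 97.5%) over assumed correlations of 0.1 to 0.7. This rests on SD 7.5 and a difference of 2. Estradiol has less need, with about 87% power unadjusted, and probably less to gain. The effect of site depends wholly on whether sites differ; under the assumed 2% to 10% of variance, type I error falls to between 4.8% and 3.9%.

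**What to change.** Add one sentence to section 8.2, or confirm that the SAP already contains it. The primary mean differences for BDI-II and estradiol are estimated by ANCOVA of the follow-up value at the primary time point on arm, baseline value of the same measure and study site, with 95% confidence intervals; the unadjusted difference is supportive. Where an outcome is transformed, as section 8.2 allows, fit the model on the transformed scale with baseline transformed in the same way.

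The sentence depends on a named primary time point. Section 4.1 gives none, and blood is drawn both at month 6 and seven days later, so the time point should be stated alongside.

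Settle this before the interim analysis in section 5.10, which falls when half the women have completed the study; covariates chosen after that look would be open to question. The cost is wording only. No new data, visits or participants are needed, and the sample size can stay as it is.

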#### Contraceptive options and unintended pregnancy in South Africa

Women in South African health services currently have limited contraceptive choices. In most cases, only oral contraceptive pills and injectable contraceptives (and more recently the etonorgestrel implant) are offered. Unfortunately, injectables have a high discontinuation rate (nearly 50% will discontinue use in 12 months), largely due to menstrual disturbances. The result of this is high rates of unintended pregnancy. In a survey of post-partum women in our East London service in South Africa, two-thirds reported that their most recent birth was unplanned. Although 79% of the women had previously used contraception, many had discontinued, 32% of whom did so due to side effects.

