## **3. Study objectives**

1. To measure differences in immunological, hormonal, physiological, psychological, behavioural and hormonal effects of NET-EN versus DMPA considered to be relevant to HIV acquisition risk and method adherence.
2. To demonstrate feasibility of a proposed large randomized clinical trial to determine the relative risk of HIV acquisition.

Primary objectives

To compare immunological, hormonal, physiological psychological and behavioural effects which may impact on HIV acquisition risk among women randomly allocated to use NET-EN with those among women allocated to use DMPA.

Secondary objectives

To compare side effects and method continuation among women allocated to use NET-EN versus women allocated to use DMPA.

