## 5.6 Sample size calculation

Primary psychological outcome: Depression

In our previous study, 24 MADRS scores in women randomized to NET-EN were 8.3 (standard deviation 7.5). Based on this standard deviation, to show a difference of 2 between the study groups with 95% certainty and 80% power would require 221 participants per group, and allowing for 15% loss to follow-up, 260 per group. (<http://pharmaschool.co/size4.asp>).

Primary biological outcome: serum 17 $\beta$  estradiol

In our previous study, 17 $\beta$  estradiol levels in women randomized to NET-EN were 136 pmol/L (standard deviation 119). Based on this standard deviation, to show a difference of 35 pmol/L in either direction between groups with 95% certainty and 80% power would require 181 participants per group, and allowing for 15% loss to follow-up, 213 per group (<http://pharmaschool.co/size4.asp>).

Because of multiple outcomes to be measured, the remaining outcome comparisons will be regarded as exploratory. In general, studies of biomarkers such as immune effects have used considerably smaller sample sizes.

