**Table 2: Study follow-up activities(Every 6months)**

---

| Activities | Staff |
|------------|-------|
|------------|-------|

|                                                      |                       |
|------------------------------------------------------|-----------------------|
| HIV counselling and test – [30min]                   |                       |
| Locator information (update)                         | Counselor             |
| Clinical interview (CRF2) - [30min]                  | Clinician/Study Nurse |
| Antropometric measures (weight) (CRF3) - [10min]     | Clinician/Study Nurse |
| Clinical assessment (CRF3) - [30min]                 | Clinician/Study Nurse |
| BDI-II & ASEX - [15min]                              | Counselor             |
| Blood and genital tract sample collection* - [10min] | Study nurse           |

Total duration of visit not more than 2 hours.

The following data will be collected at baseline, Month 6, Month 6, 7 days, Month 7.

- Age (at baseline only)
- Previous pregnancies, whether the pregnancy was intended or unintended, and the outcome of the pregnancy (at baseline only)
- Menstruation (heavy/mod/light/none) and symptoms eg pain
- Subjective concern about weight
- Feeling sad or depressed for no real reason
- "In the last 2 weeks have you felt unable to stop worrying, or thinking too much?"
- "In the last 2 weeks have you felt down, depressed or hopeless?"
- "In the last 2 weeks have you had thoughts and plans to harm yourself or commit suicide?"
- Current contraception, date of NET or DMPA injections (confirmed from patient-held family planning record if received outside the study site)
- Reason for discontinuation of allocated method
- Frequency of condom use (always/sometimes/never/not applicable)
- Number of sexual partners in previous 3 months

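### The available-case rule in section 8.2 makes no exception for method continuation or adherence, so women who stop attending and cannot be traced would, on its natural reading, leave the denominator of an outcome that their absence informs

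*Protocol*

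**What the plan says.** Section 3 makes continuation a secondary objective: "To compare side effects and method continuation among women allocated to use NET-EN versus women allocated to use DMPA". Section 4.2 lists adherence among the secondary outcomes. Of everything beyond the two primary outcomes, section 4.1 says: "The other measures will be regarded as exploratory".

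Section 8.2 announces intention to treat and then fixes one analysis set: "The primary analysis will be based on all subjects with outcome data available". No outcome is exempted. One sensitivity analysis follows: "A sensitivity analysis will be performed that only analyzes participants who have neither discontinued nor switched contraceptive methods".

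The data on continuation are listed under Table 2 in section 5.8.5, to be collected at baseline, month 6, month 6 plus 7 days and month 7: "Current contraception, date of NET or DMPA injections (confirmed from patient-held family planning record if received outside the study site"). Repeat injections are due at the research site, every 2 months for NET-EN and every 3 months for DMPA (sections 5.7.2 and 5.8.4).

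Two figures bear on size. The background says that "injectables have a high discontinuation rate (nearly 50% will discontinue use in 12 months"), and section 5.6 sets the sample size "allowing for 15% loss to follow-up, 260 per group".

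**The concern.** For estradiol or BDI-II, a missed month 6 visit is simply missing data. Continuation is different: a woman who does not come for an injection due at the site has, by not coming, given evidence about the outcome. If the rule in 8.2 is applied as written and outcome data means data from a follow-up contact, she is removed from the analysis. If such women have stopped the method more often than those who are seen, continuation is overstated.

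The single sensitivity analysis gives no help. Restricting to women who neither discontinued nor switched makes continuation 100% by construction, and it says nothing about women with no outcome recorded.

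At stake is the continuation rate that section 15 intends for counselling and family planning policy, and that would inform the larger trial whose feasibility is the second objective. The arms also attend at different intervals, so equal loss cannot be taken for granted, although the protocol gives no loss figure by arm.

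**Working it through.** **The plan's own figure.** Section 5.6 uses a difference of 2, standard deviation 7.5, 80% power and 95% certainty, taken as two-sided alpha 0.05.

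- n = 2 × (1.96 + 0.8416)² × 7.5² / 2² = 220.8, so 221 per group.
- 221 / (1 − 0.15) = 260 per group.

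Both stated figures reproduce. Since 260 × 0.85 = 221, the plan allows for 39 women per arm without outcome data. The protocol states no continuation rate at month 6 and no power for continuation, so what follows is illustrative.

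**Inputs**

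- Discontinuation at 12 months: 50%, rounding the protocol's nearly 50%.
- Discontinuation at month 6, assuming a constant rate: D = 1 − 0.5^(6/12) = 0.293.
- Loss: d = 0.15 (section 5.6).
- f: the share of lost women who had stopped. The protocol gives no value, so a range is shown.

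**Within one arm.** Discontinuation among women seen = (D − d × f) / (1 − d).

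| f | Calculation | Discontinuation among women seen | Continuation overstated by |
|---|---|---|---|
| 1 | (0.293 − 0.150)/0.85 | 16.8% | 12.5 points |
| 0.75 | (0.293 − 0.1125)/0.85 | 21.2% | 8.1 points |
| 0.5 | (0.293 − 0.075)/0.85 | 25.6% | 3.7 points |
| 0.293 | (0.293 − 0.044)/0.85 | 29.3% | 0 |

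If lost women had stopped less often than the overall rate, the error would run the other way.

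**Between arms, equal true rates.** Let D = 0.293 in both arms. With equal loss and equal f, both arms shift alike and both ratios stay at 1.00. Now assume 18% loss on NET-EN and 12% on DMPA (mean 15%), with the same f in both arms.

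| f | NET-EN discontinuation, women seen | DMPA discontinuation, women seen | Discontinuation ratio | Continuation ratio |
|---|---|---|---|---|
| 1 | (0.293 − 0.18)/0.82 = 0.138 | (0.293 − 0.12)/0.88 = 0.196 | 0.70 | 0.862/0.804 = 1.07 |
| 0.75 | (0.293 − 0.135)/0.82 = 0.193 | (0.293 − 0.09)/0.88 = 0.231 | 0.84 | 0.807/0.769 = 1.05 |
| 0.5 | (0.293 − 0.09)/0.82 = 0.247 | (0.293 − 0.06)/0.88 = 0.265 | 0.93 | 0.753/0.735 = 1.02 |

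In each of these rows the arm that loses more women looks better. In the first row the log discontinuation ratio has standard error 0.217 with 260 randomised per arm, so 0.70 lies about 1.6 standard errors from 1.00.

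**Between arms, unequal true rates.** Suppose true continuation is 55% v 65%, loss is 15% in both arms and all lost women had stopped. The continuation ratio is unchanged: (0.55/0.85)/(0.65/0.85) = 0.846. The discontinuation ratio moves from 0.45/0.35 = 1.29 to (1 − 0.55/0.85)/(1 − 0.65/0.85) = 1.50. The ratio reported therefore matters even when loss is equal.

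**The case against.** The strongest reply is that the rule may exclude nobody. Injections are due at the site and given by the research team, or documented by research staff when routine staff give them (section 5.7). A missed injection can then itself be available outcome data, and a non-attender can be classified as not continuing. That reading is possible, and so a reader who infers that the protocol definitely scores continuation only in women who are seen goes further than the text. But the protocol does not say that a non-attender counts as stopped. It lists contraception and injection dates as items gathered at follow-up contacts, and its one stated rule carries no exception. A definition of continuation may sit in an analysis plan that is not shown, but the rule stated here would still need an exemption.

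The protocol also contains safeguards. Women who stop the method stay in follow-up (section 5.9), non-attenders are traced by calls and, with consent, home visits (sections 5.8.5 and 9), and losses are compared between groups and missing values counted (section 8.2). These reduce the problem and can reveal an imbalance. They do not correct the estimate for women who remain untraced.

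The size is also open to challenge, rightly. The 15% is a sample-size allowance, not a forecast of women who stop silently. The 18% v 12% split is assumed. On the scale of the stated objective, continuation, the ratio moves only to 1.02 to 1.07.

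**Conclusion.** The point holds as a badly fitting rule, not as a demonstrated bias. An available-case set with no exception is unsuited to an outcome on which non-attendance is informative, and nothing else in section 8.2 repairs it.

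With 15% loss and 29.3% true discontinuation at month 6, the understatement of discontinuation runs from 12.5 points (all lost women stopped) through 3.7 points (half stopped) to none (lost women stopped at the overall rate). This rests on the constant-rate assumption and on the unknown behaviour of lost women. With equal true rates, a biased comparison further needs unequal loss, or unequal stopping among the lost, for which the protocol gives no figures.

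A reader might infer that continuation is certainly overstated, or that the comparison between arms would be reversed. The documents support neither: the first depends on what lost women did, and the scenario behind the ratios is a true null, so there is no direction to reverse. Continuation and adherence are exploratory, and the two primary outcomes are unaffected. The change is worth making because it is cheap and the result is meant to be used.

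**What to change.** In section 8.2, exempt method continuation and adherence from the available-case rule and state that:

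- they are analysed in all randomised women, from documented injection dates (study site, or family planning record if given elsewhere);
- a woman with no documented allocated injection covering a common time point is counted as not continuing. Month 6 is one such point, since an injection falls due then on both schedules;
- one classification window applies, prespecified by the sponsor for analysis only and defined so that it favours neither arm. The late limits in section 5.7.2 should not be borrowed: they trigger pregnancy assessment and differ by arm (more than 4 weeks for DMPA, more than 2 weeks for NET-EN);
- the available-case result is reported alongside, with a sensitivity analysis that varies the status of untraced women from all stopped to stopping at the same rate as women seen, including different rates by arm.

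The cost is a few sentences, and the injection dates are already to be collected. The downside is that some women injected elsewhere without a record will be misclassified as stopped. The tracing already planned limits this, and the sensitivity analysis shows how much it could matter.
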